## 2. Materials and Methods

We will perform an observational study using a retrospective test-negative case–control design. This method has been used successfully to estimate the effectiveness of vaccines against respiratory diseases such as influenza virus infection [25,26,27] and COVID-19 [28,29,30,31,32].

A test-negative study is considered a variant of the traditional case–control design: the study population is composed by individuals who have a predefined set of symptoms, seek help at the same healthcare unit and are tested by the same methodology, in this case, real-time reverse transcription polymerase chain reaction (rRT-PCR) or an antigen test for SARS-CoV-2. The cases are individuals who receive a positive result and controls are those with a negative result [2,33].

Patients with COVID-19-like illness admitted to the Hospital of Viana do Castelo and Hospital of Ponte de Lima from 1 June 2021 until 2 March 2022, will be enrolled. These hospitals serve a population of 231,293 people resident in the district of Viana do Castelo, located in the northern region of Portugal, as shown in Figure 2.

Patients will be eligible if they are aged 18 years old or above on the date of hospital admission, resident in the district of Viana do Castelo, meeting any of the WHO clinical criteria for COVID-19, namely acute onset of fever, cough, general weakness, fatigue, headache, myalgias, sore throat, coryza, dyspnoea, recent onset of anosmia or dysgeusia, anorexia, nausea, vomiting, diarrhoea or altered mental status who received rRT-PCR or antigen testing for SARS-CoV-2 within 10 days of illness onset.

Exclusion criteria include patients not eligible for vaccination against COVID-19 or without information on the vaccination status and without SARS-CoV-2 test results available.

Primary outcomes include (1) SARS-CoV-2 symptomatic infection, confirmed by rRT-PCR or antigen test in respiratory samples from the nasopharynx or oropharynx and (2) moderate–severe COVID-19 disease, defined by hospitalization for over 24h, intensive-care unit (ICU) admission or death.

Baseline demographic and health data are going to be collected, namely age, gender, municipality of residence, date of vaccination and type of vaccine used, number of doses, previous SARS-CoV-2 infection, and being in a clinically extremely vulnerable group due to immunodepression or respiratory disease [34]. These variables are going to be studied as potential confounders, as they may influence both the receipt of the vaccine and the occurrence of COVID-19.

The results will be compared in two periods: 1 June to 31 September 2021, corresponding to the fourth pandemic wave in Portugal and 1 November 2021 until the 2 March 2022 (fifth pandemic wave). Vaccine’s roll-out was fast in Portugal, being 50% of people fully vaccinated by 20 July 2021. Moreover, on the 22 September 2021, Portugal was the first country in the world hitting the milestone of 85% of the population fully vaccinated [35]. Initially, COVID-19 vaccines were only approved for people older than 16 (Comirnaty) or 18 years old (the other vaccines approved in the UE/EEA). In Portugal, vaccination of adolescents between 12 and 15 years old begun in August and for children from 5 to 11 years old was only approved in December of 2021. Therefore, children and adolescents under 18 years will be excluded from this study.

Data analysis will be performed using R Statistical Package^®^, Vienna, Austria (SPSS), 4.1.0 version. We will perform a descriptive analysis of all variables obtained within the scope of this research project. For continuous variables with a symmetric distribution, the mean and standard deviation are going to be used; if the distribution is not symmetric, the median and interquartile range will be chosen. Categorical variables will be described as absolute and relative frequencies.

The normal distribution of the data will be verified by visual inspection of the histogram and the Kolmogorov–Smirnov test. Baseline characteristics of cases and controls will be compared using the chi-square test, Fisher’s test, Student’s *t* test or Mann–Whitney U test, depending on the nature of the variable. The association between the vaccination status and baseline characteristics will be investigated for cases and controls. The analysis will be stratified according to age, gender, municipality of residence, date of onset of illness, date of vaccination, vaccine administered, previous SARS-CoV-2 infection, and criteria for belonging to extremely vulnerable groups [34]. The presence of interaction will be evaluated by comparing the odds ratio (OR) in the various strata for a given variable. The presence of confounding will be assessed by comparing the unadjusted and adjusted OR for each of the covariates.

Multivariate logistic regression models will be used to estimate the unadjusted and adjusted OR for each of the covariates described, considering possible confounders. Covariates were selected a priori based on their known associations with SARS-CoV-2 infection or severe disease and inoculation with a COVID-19 vaccine [33] and will be evaluated as potential confounders.

The vaccine effectiveness (EV) will be estimated from the vaccination odds ratio, adjusted for confounders (OR_ad_), between cases and controls, according to the following formula:OR = (1 − OR_ad_) × 100

The variables will be tested for multicollinearity. The presence of interaction will be verified through the likelihood test or Wald test and will be included in the model if they are significant for a significance level of 5%.

In a subsequent analysis, the vaccine effectiveness will be evaluated by the time since vaccination. The time since vaccination will be calculated by subtracting the test date from the last inoculation date. The time since vaccination will be modelled as a continuous variable.

The protocol of this study was approved by the Ethics Committee of the Local Health Unit of Alto Minho (ULSAM) with the reference number 05/2022. The ethical principles of human medical research contained in the Declaration of Helsinki, as well as national legislation, will be respected. The data collected will be aggregated and anonymized, guaranteeing the necessary confidentiality of the information collected. In addition, the principal investigator and her supervisors are subjected to medical confidentiality provided for in the Code of Ethics of the Portuguese Medical Association.

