## 3. Results

On the 14 May 2022, the data collection was still ongoing, and it is expected to be completed by June 2022. A preliminary analysis is going to be performed after finishing data collection. Currently, we have obtained data on 1329 eligible patients (652 cases and 677 controls) for both periods of the study and we plan to increase the number by 30%. We expect to obtain a vaccine effectiveness of between 40 and 70% in the prevention of symptomatic infection and 70 and 90% in the prevention of severe cases of COVID-19, according to previously described results. It is anticipated that this effectiveness may be lower in more advanced age groups due to a less-robust response of the immune system in these individuals. Additionally, we expect lower vaccine effectiveness in unvaccinated or partially vaccinated people, particularly in people with moderate-to-severe COVID-19. As the waning of VE has been previously reported [36], we believe that VE will be lower in people vaccinated with their last dose first. However, data analysis will allow us to confirm this. The results will be disseminated in national and international scientific journals in 2022–2023.

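### rRT-PCR and antigen tests are treated as one method and either negative defines a control, so missed cases can distort VE by an unknown amount

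*Protocol article*

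**What the plan says.** All of this is in the protocol article, section 2 (Materials and Methods), unless noted.

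- The design paragraph presents two assays as one method: patients are "tested by the same methodology, in this case, real-time reverse transcription polymerase chain reaction (rRT-PCR) or an antigen test for SARS-CoV-2".
- Status follows from the result alone: "The cases are individuals who receive a positive result and controls are those with a negative result".
- Eligibility accepts either assay over a fairly long window: patients "who received rRT-PCR or antigen testing for SARS-CoV-2 within 10 days of illness onset".
- The first primary outcome is likewise "confirmed by rRT-PCR or antigen test in respiratory samples from the nasopharynx or oropharynx".
- The potential confounders to be collected are "age, gender, municipality of residence, date of vaccination and type of vaccine used, number of doses, previous SARS-CoV-2 infection" and membership of an extremely vulnerable group. Test type is not listed.
- The stratifiers begin "The analysis will be stratified according to age, gender, municipality of residence, date of onset of illness, date of vaccination, vaccine administered" and end with previous infection and vulnerability. Test type is not listed here either.
- VE "will be estimated from the vaccination odds ratio, adjusted for confounders", comparing cases with controls.
- Section 3 (Results) reports "1329 eligible patients (652 cases and 677 controls) for both periods of the study", with data collection still open on 14 May 2022.

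Section 4 (Discussion) mentions misclassification of exposure only, not of the test result.

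**The concern.** In a test-negative design the test result decides who is a case and who is a control. If the two assays differ in sensitivity, a control with only a negative antigen test is more likely to be a missed case than one with a negative rRT-PCR. The article fixes the pooled rule explicitly, so this is not a detail left to a fuller document.

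When the vaccine works, missed cases bring the vaccination odds of cases into the control group and distort the odds ratio from which VE is computed. The comparison of the fourth and fifth waves is also exposed. The Discussion uses it as an indirect estimate of variant-specific VE. If the antigen share changed between waves, some of any difference in VE would come from the test mix, and an analysis that ignores test type could not show this.

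**Working it through.** **The article's own figure.** 652 + 677 = 1329, which reproduces. The article states no test-accuracy figure and no test mix, so there is nothing else to reproduce.

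**Inputs.**
- From the article: 652 positives and 677 negatives.
- Assumed: antigen-only share *f* (10–50%), antigen sensitivity *s* (0.6–0.8), rRT-PCR sensitivity 1, specificity 1, and 80% vaccinated among true controls. The article gives whole-population coverage of 50% on 20 July 2021 and 85% on 22 September 2021; 80% lies within that range.

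**Formulas, with equal sensitivity by vaccination status.**
- Overall sensitivity Se = 1 − *f* + *f·s*
- Missed cases M = 652/Se − 652
- Odds of vaccination in cases = (0.8/0.2) × (1 − VE)
- Observed VE = 1 − (odds in cases)/(odds in the 677 − M true controls plus M missed cases)

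**Worked example: *f* = 0.5, *s* = 0.7, true VE 70%.**
- Se = 0.85, and 652/0.85 = 767.1, so M = 115.1, which is 17% of 677.
- Case odds = 4 × 0.3 = 1.2, so 54.55% of cases are vaccinated.
- Vaccinated controls = 561.9 × 0.8 + 115.1 × 0.5455 = 512.3. Unvaccinated controls = 677 − 512.3 = 164.7. Control odds = 3.11.
- Observed VE = 1 − 1.2/3.11 = 61.4%.

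| *f* | *s* | Missed cases (share of 677) | True VE 70% reads | True VE 50% reads |
|---|---|---|---|---|
| 0.10 | 0.7 | 20 (3%) | 68.6% | 48.7% |
| 0.25 | 0.8 | 34 (5%) | 67.5% | 47.9% |
| 0.50 | 0.7 | 115 (17%) | 61.4% | 42.7% |
| 0.50 | 0.6 | 163 (24%) | 57.6% | 39.5% |

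Coverage matters less: at *f* = 0.5 and *s* = 0.7, a true 70% reads 64.0% with 50% coverage and 60.8% with 85%. In the latter setting, lowering antigen specificity to 0.98 moves the result by 0.3 points.

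**Unequal sensitivity (*f* = 0.5, 85% coverage).**

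| Sensitivity, unvaccinated / vaccinated | True 40% reads | True 70% reads |
|---|---|---|
| 0.8 / 0.7 | 42.4% | 67.3% |
| 0.8 / 0.6 | 48.5% | 70.3% |

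The bias shrinks and can change sign.

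**Wave comparison.** Take true VE 70% in both waves, *s* = 0.7, 80% coverage and the overall 652:677 ratio in each wave (counts by wave are not given). An antigen-only share of 10% in one wave and 50% in the other gives 68.6% against 61.4%, a gap of about 7 points from test mix alone. The shares are illustrative.

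**Dropping antigen-only negatives but keeping antigen positives.** Assume *f* = 0.5, *s* = 0.7, half of each stream true cases, true VE 70%, crude odds ratio, and coverage in non-cases of 75% in the rRT-PCR stream and 85% in the antigen stream.
- Case coverage: odds 3 × 0.3 = 0.9 (47.37%) and 5.667 × 0.3 = 1.7 (62.96%).
- Odds in detected cases = (0.5 × 0.4737 + 0.35 × 0.6296)/(0.5 × 0.5263 + 0.35 × 0.3704) = 1.164.
- rRT-PCR controls only (odds 3): VE = 1 − 1.164/3 = 61.2%.
- Pooled controls: odds (0.80 + 0.15 × 0.6296)/(0.20 + 0.15 × 0.3704) = 3.50, so VE = 66.7%.
- With the coverages swapped, detected-case odds are 1.301. Dropping antigen negatives gives 1 − 1.301/5.667 = 77.0%; pooling (control odds 3.12) gives 58.3%.
- Restricting cases and controls alike to rRT-PCR returns 70% both times.

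**The case against.** **Direction.** A reader might infer that pooling the assays necessarily pulls VE towards zero. The article does not support that. It holds if antigen sensitivity is the same in vaccinated and unvaccinated cases, and the article says nothing either way. This objection stands, so the direction must be stated conditionally.

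**Size.** A reader might take the 58% figure as the expected error. It comes from the most pessimistic pair of inputs in the first table. Nothing in the article shows that antigen-only negatives are common. At a 10–25% share the shift in a true 70% is about 1 to 2.5 points, small beside a crude 95% interval of roughly 62–76% at 652 and 677 patients with 80% control coverage. This also stands. More patients would narrow the interval but would not remove the bias.

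**Condensed article.** Confirmatory testing of antigen negatives, or the recording of test type, may be set out in a fuller protocol. Test type is an attribute of the test, so its absence from a list of baseline variables does not prove that it goes unrecorded, and that inference should not be drawn. What remains is what the article itself states: one methodology, two assays, either result decisive, and covariate and stratifier lists without test type.

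**Remedy.** Admitting only rRT-PCR-negative controls while keeping antigen positives as cases looks natural, but it takes cases from two testing streams and controls from one. The calculation shows errors in either direction. It is not always worse than pooling (77.0% against 58.3% for a true 70% in the swapped setting), but adjusting for test type cannot repair it, because the antigen stream then has no controls.

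**Conclusion.** The concern holds in conditional form. The statement of a single methodology is contradicted by the two assays named in the same sentence, and the pooled rule lets missed cases into the control group if antigen tests are the less sensitive.

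With sensitivity equal by vaccination status, 80% control coverage, perfect specificity and perfect rRT-PCR sensitivity, a true VE of 70% reads between about 69% and 58% over antigen-only shares of 10–50%. With lower sensitivity in vaccinated cases the bias shrinks or reverses. The article gives neither the antigen-only share nor the sensitivity, so the actual size and sign are unknown. A changing test mix would also affect the wave comparison. This is a worthwhile, inexpensive improvement, not a demonstrated failure of the study.

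**What to change.** 1. Take test type from the existing test record and report it by case status, vaccination status and period.
2. Include test type as a covariate or stratifier. This keeps comparisons within a testing stream and shows whether VE differs by assay; it does not remove missed cases within the antigen stream.
3. Prespecify an analysis of both primary outcomes and of the wave comparison restricted to rRT-PCR-tested patients, cases and controls alike, alongside the pooled analysis.
4. Do not exclude antigen-only negatives while retaining antigen-only positives as cases.
5. Replace the single-methodology statement with one that names two assays and says how each result is used. Add misclassification of the test result to the limitations.

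The cost is one field per patient, some wording, and wider intervals in the rRT-PCR-only analysis, which describes only patients tested that way. Data collection was still open at the date given in section 3.

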As of 10 March 2022, Portugal had over three million cumulative laboratory-confirmed cases of SARS-CoV-2, emerging from five waves of infection, as can be seen in Figure 1 [15]. Delta variant (B.1.617.2) appeared in India in December 2020 and rapidly spread worldwide, becoming dominant by August 2021 in Portugal. It has been shown to be more transmissible and virulent than the Alpha variant [16]. Additionally, a study performed in Portugal showed significantly higher odds of vaccine breakthrough infection in Delta-infected patients than in Alpha-infected, suggesting lower effectiveness of the mRNA vaccines in preventing infection with the Delta variant [17], which is consistent with other studies [18,19].

The B.1.1.529 (Omicron) variant was first found in South Africa in November 2021, and it quickly spread worldwide. Omicron variant was shown to be 2.8-times more infectious than the Delta [20] and was responsible for the fifth pandemic wave in Portugal, which reached its peak on the 25 January 2022 with 5598 cases per million inhabitants. Omicron has shown immunity escaping capacity in laboratory studies and booster vaccine doses may be essential to overcome this [21,22].

This article presents the study protocol for evaluating the effectiveness of vaccines against COVID-19 in the prevention of symptomatic and severe disease in a district located in the northern region of Portugal, using a retrospective test-negative case–control design.

We will perform a comparative analysis between the fourth pandemic wave (1 June to 30 September 2021), dominated by Alpha and Delta variants and the fifth pandemic wave (1 November 2021 to 2 March 2022), Omicron-dominant, represented in Figure 1. In the beginning of the first period, the Alpha variant was dominant in Portugal, and by the week of 21 to 27 June 2021, the Delta variant became dominant [23]. The fifth wave of infection in Portugal, corresponding to our second period in analysis, was dominated by the Omicron variant since the week of 20 to 26 December 2021 [24].

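### The severe-disease outcome is defined by level of care with no link to COVID-19 as the cause, so incidental infections pull severe-disease VE towards VE against infection

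*Protocol article*

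**What the plan says.** Section 2 (Materials and Methods) defines the second primary outcome as "moderate–severe COVID-19 disease, defined by hospitalization for over 24h, intensive-care unit (ICU) admission or death". Case status depends on the test alone: "The cases are individuals who receive a positive result and controls are those with a negative result".

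The clinical filter acts at entry. Patients qualify by "meeting any of the WHO clinical criteria for COVID-19, namely acute onset of fever, cough, general weakness, fatigue, headache", and the list goes on to "anorexia, nausea, vomiting, diarrhoea or altered mental status who received rRT-PCR or antigen testing for SARS-CoV-2 within 10 days of illness onset". One symptom is enough. The exclusions ("Exclusion criteria include patients not eligible for vaccination against COVID-19 or without information on the vaccination status", and no available test result) do not cover a different main diagnosis.

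VE is then compared between two periods: "We will perform a comparative analysis between the fourth pandemic wave (1 June to 30 September 2021), dominated by Alpha and Delta variants", and the Omicron-dominant fifth wave. Section 3 (Results) expects a VE of 40–70% against symptomatic infection and 70–90% against severe disease. The limitations in section 4 (Discussion) do not mention incidental infection.

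**The concern.** The outcome's name is specific to COVID-19, but its definition is not. A patient with a stroke and altered mental status, a bowel disorder with vomiting, or heart failure with dyspnoea passes the symptom filter. If that patient also tests positive and stays more than 24 hours, the stay counts as moderate–severe COVID-19. Vaccination cannot prevent that admission; it can only prevent the infection found alongside it.

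The estimate labelled severe-disease VE is therefore a mixture of true severe-disease VE and VE against infection. The protocol expects the second to be lower, so the mixture reads too low. The result is meant to inform booster decisions, and the comparison of the two periods is the study's main question. A drop between periods could therefore come partly from the outcome definition.

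**Working it through.** The article gives no sample-size or precision figure for this outcome, so there is no stated number to reproduce. The check is a mixture calculation.

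**Inputs**
- True severe-disease VE (VE_s): 80% and 90%, within the 70–90% expected in section 3.
- VE carried by incidental infections (VE_i): 40% and 70%, the limits expected in section 3 for symptomatic infection. Using them for incidental positives is an assumption.
- Coverage v: 85%, the population figure given in section 2 for 22 September 2021, used here as the vaccinated share of controls.
- F, the incidental share of all coded-severe cases: 10%, 20% and 30%. This is an assumption; the article has no figure.

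**Formulas**
- Let f be the incidental share among unvaccinated coded-severe cases. The observed odds ratio is (1 − f)(1 − VE_s) + f(1 − VE_i), so observed VE = VE_s − f(VE_s − VE_i).
- Conversion from F: f = F·a / [F·a + (1 − F)·b], with a = 1 − v·VE_s and b = 1 − v·VE_i.

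**One case in full** (VE_s 80%, VE_i 40%, F 20%)
- a = 1 − 0.85 × 0.80 = 0.32; b = 1 − 0.85 × 0.40 = 0.66.
- f = 0.064 / (0.064 + 0.528) = 0.108.
- Observed VE = 0.80 − 0.108 × 0.40 = 75.7%.

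**All cases** (observed VE)

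| True VE_s | VE_i | F = 10% | F = 20% | F = 30% |
|---|---|---|---|---|
| 80% | 40% | 78.0% | 75.7% | 73.1% |
| 80% | 70% | 79.2% | 78.4% | 77.5% |
| 90% | 40% | 88.1% | 85.9% | 83.4% |
| 90% | 70% | 88.8% | 87.5% | 86.0% |

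If VE_i were 0, a true 80% would read 77.3%, 74.1% or 70.4%. If VE_i equals VE_s (both 70%), there is no bias.

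**Comparison of periods**

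With VE_s held constant, the bias f(VE_s − VE_i) changes only if f or VE_i changes.
- *Only VE_i changes* (70% in the fourth wave, 40% in the fifth, same f): the false fall is f × 30 points, which is 3 points at f = 10% and 6 points at f = 20%. At 85% coverage, VE_s 80% and VE_i 40%, f = 10% corresponds to F = 0.10 × 0.66 / (0.90 × 0.32 + 0.10 × 0.66) = 0.066 / 0.354, about 19%.
- *F is 5% in both waves* (coverage 50% in the fourth, the July 2021 figure in section 2, and 85% in the fifth; VE_s 70–90%): with VE_i 40% in both, observed VE rises by 0.3–0.8 points. With VE_i going from 70% to 40%, it falls by 0.1–0.9 points.
- *F rises from 5% to 10–30%* and VE_i goes from 70% to 40%: the false fall is 1.6–6.4 points at a true 80% and 1.1–5.8 points at a true 90%. Most of this fall comes from the assumed rise in F.

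**The case against.** **The entry filter is narrower than none.** Acute onset of a listed symptom and a test within 10 days of onset remove the symptom-free positive found by admission screening. This stands and limits the incidental share. It does not remove patients acutely ill from something else, because one non-specific symptom suffices.

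**A care-level definition is objective, and recorded cause has its own errors.** Decompensation of a chronic disease triggered by COVID-19 may be coded to the chronic disease, and coding may vary with known vaccination status. This stands, and it argues against replacing the stated definition outright. It does not argue against reporting a second version beside it.

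**A condensed article may leave adjudication to the full protocol.** That would hold for operational detail. Here the article states the primary outcome definition itself, and as stated it has no attribution.

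**A reader might go further and infer that high incidence in the Omicron wave must dilute severe-disease VE mainly in that period.** The fifth wave is described as one "which reached its peak on the 25 January 2022 with 5598 cases per million inhabitants". The article does not support that inference. Higher prevalence raises the proportion of other-cause admissions that test positive, but it also raises true severe COVID-19 admissions. Write i for incidence, d for duration of positivity, A for the rate of other-cause admissions with a qualifying symptom, and s for severe risk per infection. Then f = i·d·A / (i·d·A + i·s) = d·A / (d·A + s), and incidence cancels. The incidental share rises if severe risk per infection falls, and no section says that it did. The peak is also a single date within a period running from 1 November 2021 to 2 March 2022, Omicron dominated only from late December, and the text gives no fourth-wave incidence to compare.

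**Conclusion.** The point holds as a specificity problem in the second primary outcome. As defined, it mixes severe COVID-19 with other illness in symptomatic test-positive patients, and this biases severe-disease VE towards VE against infection whenever the latter is lower. Under the stated assumptions the loss is about 1–2 points at a 10% incidental share and about 3–7 points at 30%. The size rests on an incidental share that the article does not give and on illustrative values for coverage and VE against infection.

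The bias can be present in either period. A false difference between periods is possible, for example if immune escape lowered VE against infection or if severity per infection fell. Section 1 (Introduction) reports laboratory evidence for the first and says nothing on the second. That a false fall will occur, or that the 5598 peak shows one, cannot be concluded from the article.

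**What to change.** While data collection is open, as section 3 describes it, add one field: the recorded main reason for admission or cause of death. Report outcome 2 in both periods in two versions:
- as now defined;
- restricted to stays over 24 hours, ICU admissions and deaths attributed to COVID-19.

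State in advance that a pre/post-Omicron fall in severe-disease VE will be claimed only if it also appears in the attributed version. Add incidental infection to the limitations.

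The cost is one more abstracted item, fewer events and so wider intervals in the restricted version, and possible coding error, including COVID-19-triggered decompensation coded to the chronic disease. Keeping the stated definition alongside shows how much the conclusion depends on attribution.

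### Date of vaccination, vaccine type and number of doses are named as potential confounders, and the first two as stratifiers, although all three are components of the exposure

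*Protocol article*

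**What the plan says.** Section 2. Materials and Methods of the Protocol article lists the baseline data, "namely age, gender, municipality of residence, date of vaccination and type of vaccine used, number of doses, previous SARS-CoV-2 infection", together with membership of a clinically extremely vulnerable group. It gives the whole list one role: "These variables are going to be studied as potential confounders". The reason offered is that each of them could affect both whether a person is vaccinated and whether that person develops the disease.

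The later analysis paragraphs of the same section use the variables in three ways:

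- The stratification list includes "date of onset of illness, date of vaccination, vaccine administered, previous SARS-CoV-2 infection". Number of doses is not in that list.
- The strata serve to judge interaction: "The presence of interaction will be evaluated by comparing the odds ratio (OR) in the various strata for a given variable".
- Logistic models are to "estimate the unadjusted and adjusted OR for each of the covariates described, considering possible confounders", and VE is one minus the confounder-adjusted vaccination OR, times 100.

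Confounding is judged by comparing unadjusted with adjusted ORs. The variables are also to be tested for multicollinearity, with no action attached. VE by time since vaccination is a separate, later analysis with time as a continuous variable.

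**The concern.** A confounder must be able to affect both whether a person is vaccinated and whether that person becomes a case. Date, product and number of doses exist only once vaccine has been given. An unvaccinated patient has no date, no product and zero doses. For these three variables the stated reason is therefore wrong, and adjusting for them conditions on the exposure itself.

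Every VE in the study is derived from the adjusted vaccination OR. If these variables enter the adjustment set, that OR either cannot be estimated or no longer compares vaccinated with unvaccinated patients. This is a role that the article assigns to named variables, so it is not a detail left to a fuller document.

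**Working it through.** The article gives no figure that depends on this choice, so there is none to reproduce. Steps 1 and 2 concern structure and need no assumed effect sizes. Steps 3 and 4 rest on assumptions.

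**1. Doses or product as a factor.** Take the columns intercept, vaccinated (yes/no), dose = 1, dose = 2, dose = 3. Every vaccinated patient is in exactly one dose group, so vaccinated = (dose = 1) + (dose = 2) + (dose = 3). Five columns, rank 4. With four products instead: six columns, rank 5. With both: nine columns, rank 7. In each case the vaccination coefficient is not identifiable.

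**2. Strata.** A stratum defined by a product or by a vaccination date contains vaccinated patients only. One row of the vaccinated-by-case table is empty, so there is no OR against the unvaccinated to compare across strata.

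**3. Doses as a count (0 for unvaccinated).** The model has full rank and can be fitted.

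Inputs:
- Sample size from 3. Results: 652 + 677 = 1,329 patients, plus 30%: 1,329 × 1.3 ≈ 1,728.
- Assumed: 20/10/50/20% with 0/1/2/3 doses, and odds of being a case of 1.6 in the unvaccinated.
- Assumed: dose-specific ORs as in the table.

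Worked example, ORs 0.70/0.45/0.25:
- P(case) = odds/(1 + odds) with odds = 1.6 × OR, giving 0.615, 0.528, 0.419 and 0.286 for 0, 1, 2 and 3 doses.
- Average in the vaccinated: (0.1 × 0.528 + 0.5 × 0.419 + 0.2 × 0.286)/0.8 = 0.399.
- Vaccination term alone: OR = (0.399/0.601)/1.6 = 0.415, so VE = 58%.
- Vaccination term plus dose count, fitted to the expected counts: vaccination OR 1.26, OR per dose 0.59. Check: 1.26 × 0.59 = 0.74, 1.26 × 0.59² = 0.44 and 1.26 × 0.59³ = 0.26, close to the inputs 0.70, 0.45 and 0.25. The vaccination term alone gives (1 − 1.26) × 100 = -26%. It is the dose line extrapolated back to a vaccinated person with zero doses, and no such person exists.

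The same calculation for other assumed ORs:

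| ORs for 1/2/3 doses | VE, vaccination term alone | VE, dose count added |
|---|---|---|
| 0.45/0.45/0.45 | 55% | 55% |
| 0.50/0.45/0.40 | 56% | 44% |
| 0.60/0.40/0.35 | 59% | 32% |
| 0.70/0.45/0.30 | 57% | -5% |
| 0.70/0.45/0.25 | 58% | -26% |

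At n = 1,728 the standard error of the log OR rises from about 0.12 to about 0.23, even in the row where VE does not move.

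**4. Direction.** A separate simulation used 300 runs of 1,728 patients, 80% vaccinated, ORs 0.70/0.45/0.30, waning of 0.003 log-odds per day, and unvaccinated patients coded 0. VE was 58% with the vaccination term alone, -6% with dose count added, 72% with time since vaccination added, and 28% with both. The shift can go either way.

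**5. Safeguards in the text.** The multicollinearity test has no stated consequence and does not protect the exposure term. The comparison of unadjusted with adjusted ORs works against the study: whenever there is a dose gradient, dose count moves the OR, so it looks like a confounder to keep.

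**The case against.** The strongest reply is that the damaging model is possible under the text but not specified by it. The variables are only to be studied and evaluated as potential confounders. No passage fixes a final model with a yes/no vaccination term beside number of doses, and the levels of vaccination status are not defined. This stands, and it limits the point to a conditional one.

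A second reply is that stratifying by vaccine administered may mean product-specific VE, each product against the unvaccinated, which would be legitimate. That reading is possible, but the article names no common unvaccinated reference and describes comparing ORs across strata.

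A third is that a rank-deficient model or an empty stratum fails visibly and does not yield a wrong published VE. That is true of factor coding and strata. It is not true of a dose count, which fits without warning.

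A fourth is that the size depends on coding and dose gradient. This also stands: with equal ORs nothing moves, and -26% is the unfavourable end of the scenarios tried.

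A reader might also infer more than the article supports:

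- Number of doses is not a stratifier. It appears only in the confounder list.
- The sentence in 3. Results, "Additionally, we expect lower vaccine effectiveness in unvaccinated or partially vaccinated people", is loosely worded, since the unvaccinated are the natural reference. It states an expectation, specifies no analysis, and does not show that the reference group is unfixed.
- The absence of a lag between dose and protection is a separate matter that a condensed article may leave to the full protocol.

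**Conclusion.** The point holds in conditional form. The article gives three components of the exposure a confounder role that they cannot have, and uses two of them as stratifiers. Without any assumed effect size, factor coding makes the vaccination coefficient unidentifiable, and product or vaccination-date strata give no OR against the unvaccinated. With doses as a count, the coefficient stops measuring vaccinated versus unvaccinated. Under the assumed dose mix, VE of 55–59% becomes 55%, 44%, 32%, -5% or -26% as the dose gradient steepens, with the standard error nearly doubled.

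A reader might conclude that the study will report a null or harmful vaccine. The documents do not support that. It would need a dose count beside a yes/no vaccination term and a steep dose gradient, and the article commits to neither.

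**What to change.** In 2. Materials and Methods:

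- Remove date of vaccination, type of vaccine and number of doses from the variables called potential confounders.
- Remove date of vaccination and vaccine administered from the stratification list.
- State that number of doses, product and time since last dose define exposure levels, each compared with one common unvaccinated reference.
- Limit adjustment to age, gender, municipality, calendar date of onset, previous infection and clinical vulnerability.

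The variables needed are already named in the article. The cost is analysis wording only, with no new data and no change to recruitment.
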